### Data management plan

All data collectors (i.e., research assistants) will login to REDCap (a secure web application) to enter the participants’ responses using the participant’s unique study ID. The use of REDCap significantly reduces errors in data collection and the amount of missing data. REDCap will be accessed using university iPads, desktop computers or encrypted laptops dedicated to the study. The digitally recorded qualitative interviews will be labeled with each participant’s study ID and uploaded to the secure password protected SharePoint site. The transcriptionist will also have access to this site and will upload all transcripts to this site as well. The Research Coordinator and site PI’s will also have access to this site. There will be no sharing of individual data because of consent procedures.

### Data analysis

All data will be cleaned and checked for completeness and accuracy. Qualitative data from the interviews will be transcribed verbatim by an experienced transcriptionist.

#### Outcome analysis

Outcome analysis will include descriptive statistical analysis of data as well as analysis to understand the effect of MT4C-In Care on primary and secondary outcomes. To assess the impact of MT4C-In Care on the MCS, the primary outcome, we will use generalized estimating equations (GEE), and will run models using PROC GENMOD in SAS Version 9.3 [42]. The SF-12v2 MCS score is a continuous variable. Variables included in the GEE model will be group (intervention, control), time (baseline, 2 months, 4 months), and a group x time interaction term, which tests the hypothesis that MT4C-In Care promotes better mental health at 2 months and 4 months in the intervention as compared to the control group [43]. If a significant intervention effect is detected in this model, additional covariates (e.g., age, gender) will be added to adjust for statistically significant baseline differences observed in demographic characteristics between the intervention and control group. To model time, we will plot the mean MCS values in each group at each time period. Time will be included as either a continuous variable (if the plot suggests a linear trend) or a categorical variable (if the plot suggests a non-linear trend).

A key advantage of GEE, as compared to linear regression, is that no assumption is made that data are normally distributed. SAS allows the user to choose the most appropriate distribution and link function. In this study, we will select link function that is a best fit for the distribution of the participants’ MCS scores. If we observe a negative skew in MCS scores (as is the case in many populations), we will use a reflected transformation which can normalize the data [44], allowing for use of the identify link function which is used with a normal distribution.

While outcome analysis will follow the intent to treat principle, sensitivity analyses will also be completed to assess impact of the intervention upon outcomes with level of use as a covariate. The aim of the latter analysis is to explore whether amount of use of MT4C-In Care influences the impact of the intervention upon outcomes.

GEE assumes that data are missing completely at random [43]. This is difficult to verify [45], and data missingness more likely reflects a continuum from missing at random to missing not at random [46]. Despite this, experts recommend basing the primary analysis on the missing at random assumption [47]. We will use multiple imputation to handle missing data and will then analyze each dataset using GEE to determine the best method for handling missing data.

Analyses of secondary outcomes (hope, self-efficacy, grief, loneliness, and social support) will follow the same approach as for the primary outcome. An appropriate method for handling missing data for analysis of secondary outcomes will be selected based on observed missing patterns.

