### Power and sample size

We aim to recruit a convenience sample of 280 participants, 140 in each of the intervention and control groups. Our design for the outcome analysis includes three repeated measurements to observe how the change in outcomes over time differs between the intervention and control group. This sample size achieves 89% power to detect a 15% difference in the mental health summary score between the two groups over time, when alpha level is 5%. This calculation assumed a Compound Symmetry covariance structure, a proportion of 30% in group 2, and correlation between observations on the same subject of 0.50.

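### The primary GEE estimates a difference in change from baseline and does not adjust for baseline MCS, which is valid but inefficient: at the protocol's correlation of 0.50, adjustment would cut the variance by 25% to 33%

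*Protocol article*

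**What the plan says.** The Outcome analysis section lists the terms of the primary model: "Variables included in the GEE model will be group (intervention, control), time (baseline, 2 months, 4 months), and a group x time interaction term". The inference rests on the interaction, "which tests the hypothesis that MT4C-In Care promotes better mental health at 2 months and 4 months in the intervention as compared to the control" arm. The outcome is treated as continuous ("The SF-12v2 MCS score is a continuous variable").

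Baseline MCS is not named as a covariate. The only adjustment described is conditional and concerns demographic characteristics that differ significantly between groups at baseline: "If a significant intervention effect is detected in this model, additional covariates (e.g., age, gender) will be added". The coding of time is left to a plot of the means: "Time will be included as either a continuous variable (if the plot suggests a linear trend) or a categorical variable". The five secondary outcomes follow the same approach.

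The Power and sample size section gives the design figures. On numbers and allocation it states: "We aim to recruit a convenience sample of 280 participants, 140 in each of the intervention and control groups". On the measurement schedule it adds: "Our design for the outcome analysis includes three repeated measurements". The calculation assumes compound symmetry and a "correlation between observations on the same subject of 0.50".

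**The concern.** With baseline as one level of time and an unconstrained group main effect, the model spends information on estimating a baseline difference between the groups. The interaction then subtracts the whole observed baseline difference from each follow-up difference. When the within-subject correlation is below 1, subtracting all of it adds noise that a regression on baseline would not. At a correlation of exactly 0.50, the change contrast at one visit is no more precise than comparing follow-up scores and ignoring baseline.

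What is at stake is power on the primary outcome. The Background section reports that the feasibility study (37 participants) did not detect a significant difference in mental health, so there is little reason to give precision away. Because the secondary outcomes use the same model, the loss carries over to them.

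**Working it through.** **Inputs.** From Power and sample size: n = 140 per group, three measurements, compound symmetry, correlation ρ = 0.50, alpha 5%. From Outcome analysis: the model terms. Assumed here: complete data (no dropout figure is given), identity link, two-sided test.

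**The plan's own figure.** The stated 89% reproduces as a time-averaged comparison of two proportions, 30% versus 45%. The averaging factor is (1 + 2 × 0.50)/3 = 0.667, so the effective n is 140/0.667 = 210 per group. The pooled SE is √(2 × 0.375 × 0.625/210) = 0.0472 and the unpooled SE is √((0.45 × 0.55 + 0.30 × 0.70)/210) = 0.0467. Power = Φ((0.15 − 1.96 × 0.0472)/0.0467) = 89.1%. This is not the power of the planned interaction test on a continuous MCS, so 89% says nothing about the precision examined below. The 0.50 is nevertheless the only within-subject correlation the protocol offers.

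**Variance of the treatment contrast, in units of 2σ²/n.**

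- One follow-up visit, as planned: 2(1 − ρ) = 2 × 0.50 = 1.00. A follow-up comparison that ignores baseline is also 1.00.
- One follow-up visit, adjusted for baseline: 1 − ρ² = 1 − 0.25 = 0.75. Reduction 25%.
- Mean of 2 and 4 months, as planned: (1 + ρ)/2 + 1 − 2ρ = 0.75 + 1 − 1 = 0.75.
- Mean of 2 and 4 months, adjusted: (1 + ρ)/2 − ρ² = 0.75 − 0.25 = 0.50. Reduction 33%.

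The ratios of standard errors are √0.75 = 0.87 and √(0.50/0.75) = 0.82, so 13% and 18% smaller. In sample-size terms, 280/0.75 ≈ 373 participants analysed as planned would match 280 analysed with adjustment at a single visit. If time is coded as linear, the reduction is 27%. For the two-degree-of-freedom joint interaction test with equal effects at both visits it is 33%. A simulation of 8,000 trials of 280 participants at ρ = 0.50 gave 25.0% (one visit) and 33.5% (mean).

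**Dependence on the correlation.**

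| ρ | One visit, planned to adjusted | Reduction | Two-visit mean, planned to adjusted | Reduction |
|---|---|---|---|---|
| 0.4 | 1.20 to 0.84 | 30% | 0.90 to 0.54 | 40% |
| 0.5 | 1.00 to 0.75 | 25% | 0.75 to 0.50 | 33% |
| 0.6 | 0.80 to 0.64 | 20% | 0.60 to 0.44 | 27% |
| 0.7 | 0.60 to 0.51 | 15% | 0.45 to 0.36 | 20% |
| 0.8 | 0.40 to 0.36 | 10% | 0.30 to 0.26 | 13% |

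**Illustrative power.** The protocol gives no SD for MCS and no effect in SD units, so 0.3 SD is an assumption. Power is Φ(0.3/SE − 1.96), with SE = √(factor × 2/140) and ρ = 0.50.

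- One visit: SE 0.1195 gives 71% as planned; SE 0.1035 gives 83% adjusted.
- Two-visit mean: SE 0.1035 gives 83% as planned; SE 0.0845 gives 94% adjusted.

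For an assumed 0.25 SD the pairs are 55% to 68% and 68% to 84%. For 0.35 SD they are 83% to 92% and 92% to 99%.

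**The case against.** The strongest objection concerns the order of events. Under Recruitment and randomization, the research assistant reads a consent form specific to the assigned group, and baseline measures are collected only after that. Baseline MCS therefore follows assignment and arm-specific consent. A reader might infer that randomisation makes the baseline difference zero in expectation, so that the group main effect can be dropped at no risk. The documents do not secure that: who consents, or how they answer, could differ by arm. If a true baseline difference of 0.10 SD (assumed) persisted, an adjusted or equal-baseline estimate would be off by (1 − 0.50) × 0.10 = 0.05 SD and the change contrast by nothing. If the difference were present only at baseline, the change contrast would be off by 0.10 SD and the adjusted estimate by 0.05 SD. Neither analysis dominates. This stands and limits the remedy. It does not remove the efficiency loss, and the study materials are sent only after the baseline interview, so baseline precedes exposure to the intervention.

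It is also fair to say that the interaction matches the stated hypothesis, which is worded as change from baseline relative to control, and that the link function and a reflected transformation are left open, so the variances are exact only for an identity link. Both are true. Baseline adjustment still compares the same groups at the same visits, and the loss appears under either coding of time. Multiple imputation of missing scores does not supply the adjustment, since the free group term remains.

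**Conclusion.** The point holds as a matter of efficiency. The stated primary model gives up 25% of the variance per visit and 33% for the two-visit mean at ρ = 0.50, under compound symmetry, complete data and an identity link.

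Three stronger readings are tempting and not supported. First, a reader might infer that the planned test is biased or exposed to baseline imbalance. Over randomisations it is unbiased; only conditional on an observed baseline difference d does its expectation shift, by −(1 − ρ)d. Second, the loss is not a fixed quarter to a third. It depends on ρ, and the protocol's 0.50 belongs to a calculation that reproduces only for proportions, so it is weak evidence about MCS. At 0.8 the loss is 10% to 13%. Third, the power gains are not the protocol's own shortfall, because the 0.3 SD effect behind them is assumed.

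The change is worth making but is not a condition for a valid trial. If a separate analysis plan already adds baseline MCS, the point is closed.

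**What to change.** Replace the primary model with one for MCS at 2 and 4 months, containing group, categorical visit, group by visit, baseline MCS and baseline by visit. Read the 2-month and 4-month group contrasts from it. Do the same for hope, self-efficacy, grief, loneliness and social support, each with its own baseline score.

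Keeping all three visits and dropping the group main effect, so that baseline means are equal, is an alternative under two conditions. The working correlation must not be independence, which at ρ = 0.50 returns the variance factor to 1.00. And the team must be able to show that the baseline interview is unaffected by allocation, given that it follows assignment and arm-specific consent. The covariate model is not immune to a real, persistent baseline difference either, so keep the planned change contrast as a named sensitivity analysis and report the baseline means by group.

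No new data are needed. The cost is revised model wording and an amendment to the ethics boards. Because the research team itself sees interim analyses every 6 months, the wording should be settled before outcome results by group are examined.

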**Methods:**

This study is a single blinded pragmatic mixed methods randomized controlled trial. Approximately 280 family carers of older persons (65 years of age and older) with dementia residing in LTC will be recruited for this study. Data will be collected at three time points: baseline, 2 month, and 4 months. Based on the feasibility study, *we hypothesize that participants using MT4C-In Care will report significant increases in hope, general self-efficacy, social support and mental health quality of life, and significant decreases in grief and loneliness from baseline, as compared to an educational control group*. To determine differences between groups and over time, generalized estimating equations analysis will be used. Qualitative descriptive analysis will be used to further evaluate MT4C-In Care and if it supports carers through transitions.

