### Purpose

The purpose of this study is to evaluate whether use of MT4C-In Care over 2 months is effective to decrease loneliness and grief, and increase hope, general self-efficacy, social support and mental health as compared to an educational control group. It will address the following research questions:
Is there a 2 month (immediately post-intervention) and 4 month (2 months post-intervention) increase in mental health, general self-efficacy, social support and hope, and decrease in grief and loneliness, in carers of a person living with dementia residing in LTC using MT4C-In CARE compared to an educational control group?Do carers of persons living with dementia residing in LTC perceive My Tools 4 Care- In Care helps them with the transitions they experience?

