### Educational control group

The educational resource that will be emailed to the control group participants is an Alzheimer Society document called *Progression* [26] immediately following baseline interviews*.* This document was developed for use by people with dementia and their family and friend carers. It provides a summary overview of the stages of the disease, importance of person-centred care, prompts to access support, and a list of additional resources. It is available for free on the Alzheimer Society of Canada website. Following data collection, control group participants will also be granted access to MT4C-In Care.

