### Intervention: my tools 4 care-in care

The intervention group will receive via email the educational resource provided to the control group and instructions on how to access to the MT4C-In Care site immediately following baseline interviews. MT4C-In Care access will occur for 2 months via an assigned web link and unique username and password. Participants will access the MT4C-In Care tool as frequently as desired, and will choose which content to engage with. They may choose not to access MT4C-In Care at any time. Some activities prompt the participants to enter information into the site, and this information will not be accessed by anyone, including the research team. The components of MT4C-In Care include a home page which introduces the toolkit and sections: a) “About Me” (contains guided evidence-based activities), b) “Common Changes to Expect”, c) “Frequently Asked Questions”, and d) Resources. More detailed information about My Tools 4 Care-In Care is published elsewhere [24].

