#### Outcome measures

The **Mental Component Summary (MCS) score**, short form Health Survey (SF-12v2) [28], is the primary outcome because MT4C-In Care aims, ultimately, to support carers’ psychological well-being [29]. The higher the score on the MCS, the higher the mental health. The **SF-12v2** measures perceived function and well-being with 12 items using a variety of Likert scales. A majority of carers are older adults, and the SF-12v2 has been used with community-dwelling older adults. The tool’s eight domains (physical functioning, role-physical, bodily pain, general health, vitality, social functioning, roles, and emotional and mental health) can be combined to derive scores (maximum 100) for a physical component summary (PCS) and mental component summary (MCS). The SF-12v2 is used widely and in a variety of populations, and evidence supports its internal consistency, reliability, and construct validity [30, 31].

We selected as secondary outcomes those variables which are the hypothesized mechanisms by which MT4C-In Care affects mental health including hope, general self-efficacy, social support, grief and loneliness. Therefore, these are the proposed proximal outcomes targeted by MT4C-In Care. Measures of hope, self-efficacy, grief, loneliness, and social support are:

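### One group x time interaction is said to test better MCS at both 2 and 4 months, but neither permitted coding of time tests that hypothesis

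*Protocol article*

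**What the plan says.** The Purpose section asks about two occasions with different meanings: "Is there a 2 month (immediately post-intervention) and 4 month (2 months post-intervention) increase in mental health". The intervention section limits use of the tool to the first of these periods: "MT4C-In Care access will occur for 2 months via an assigned web link and unique username and password". Controls wait until the end: "Following data collection, control group participants will also be granted access to MT4C-In Care". The 2-month visit is therefore a randomized comparison at the end of access, and the 4-month visit is a randomized comparison two months after access ends.

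The MCS "is the primary outcome because MT4C-In Care aims, ultimately, to support carers’ psychological well-being", with no time point attached. The hypothesis in the abstract gives none either; it ends with "significant decreases in grief and loneliness from baseline, as compared to an educational control group". The power statement refers only to a difference over time.

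The Outcome analysis section lists the model terms as "group (intervention, control), time (baseline, 2 months, 4 months), and a group x time interaction term" and says of the interaction: "which tests the hypothesis that MT4C-In Care promotes better mental health at 2 months and 4 months in the intervention as compared to the control". Covariates are added if that model shows a significant intervention effect, which is not tied to either visit. The coding of time is decided from the plotted group means: "Time will be included as either a continuous variable (if the plot suggests a linear trend) or a categorical variable".

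**The concern.** The section gives one test a conclusion about two visits. Rejecting an interaction null shows that the arms differ somewhere in their change over time. It does not show that the intervention arm is better at the end of access and still better two months later. Those are the two questions that the Purpose section asks, and they matter differently to anyone deciding whether to offer the tool: one is about effect while it is available, the other about persistence.

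If the sentence stands, a significant interaction can be reported as support for benefit at both visits when the data show it at one. The Outcome analysis section applies the same approach to the five secondary outcomes, so the same reading would carry over to them.

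**Working it through.** **Inputs.** From Power and sample size: 140 per arm, three measurements, compound symmetry, within-person correlation ρ = 0.50, alpha 5%, 30% in group 2, a 15% difference, 89% power. Assumed because the documents give no figure: effects in SD units from 0.2 to 0.5, complete data, two-sided tests.

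**The plan's own figure.** The 89% reproduces as a time-averaged difference of two proportions, 45% against 30%.
- Variance factor: [1 + (m − 1)ρ]/m = (1 + 2 × 0.5)/3 = 0.667, so the effective n is 140/0.667 = 210 per arm.
- SE under the null: √(2 × 0.375 × 0.625/210) = 0.0472. SE under the alternative: √((0.2475 + 0.21)/210) = 0.0467.
- Power: Φ[(0.15 − 1.96 × 0.0472)/0.0467] = Φ(1.23) = 0.891.

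This averages over visits and isolates neither 2 nor 4 months. For a single visit with 140 per arm the same formula gives 0.739. A change-from-baseline contrast has variance factor 2(1 − ρ) = 1, so it also has about 74%.

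**Categorical time.** Let d2 and d4 be the between-arm differences in change at 2 and 4 months, in SD units.
- Variance of each: v = 2 × 2(1 − 0.5)/140 = 0.01429, so SE = 0.1195.
- Covariance: 2(1 − 0.5)/140 = 0.00714, so their correlation is 0.5. This holds for any ρ under compound symmetry.
- Noncentrality of the 2-df test: λ = (d2² − d2·d4 + d4²)/(0.75v).
- Sustained (d, d), transient (d, 0) and delayed (0, d) each give d²/(0.75v) = 93.3d².

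At 0.3 SD, λ = 93.3 × 0.09 = 8.4 for all three patterns, so the test has identical power for each.

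**Continuous time.** With visits at 0, 2 and 4 months the slope contrast has weights (−1, 0, 1), which is the 4-month change contrast. A transient effect contributes nothing to it, so rejection occurs only at the 5% error rate.

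| Effect (SD) | 2-df test: sustained, transient or delayed | Transient: 2-month contrast | Transient: 4-month contrast | Transient: slope test | Transient: significant 2-df tests with non-significant 4-month contrast |
|---|---|---|---|---|---|
| 0.2 | 39% | 39% | 5% | 5% | 89% |
| 0.3 | 74% | 71% | 5% | 5% | 93% |
| 0.4 | 94% | 92% | 5% | 5% | 95% |
| 0.5 | 99% | 99% | 5% | 5% | 95% |

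The last column is from 400,000 simulated trials per effect size.

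**Reading the two visit contrasts separately.** With contrast correlation 0.5 and no effect at either visit, the chance that at least one has p < 0.05 is 0.0908 (one million simulated trials). The chance that both do is 0.05 + 0.05 − 0.0908 = 0.0092.

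**The case against.** Four arguments on the other side deserve weight.

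First, this is a condensed journal article, and a primary time point, named contrasts and a testing order may be in an analysis plan that is not shown. Their absence is therefore not the finding. What stands is the sentence that is in the article, which pairs a test with a conclusion the test cannot give.

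Second, a reader might infer that the plan will declare a transient gain as lasting benefit. The documents do not support that without qualification. Under continuous time the test would mostly miss a transient effect. The risk arises under categorical time, although a rise and fall in the plotted means is the pattern likely to lead to that coding.

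Third, a reader might infer that the planned model cannot separate the two visits, or that a gain followed by harm would pass as benefit. With categorical time the model contains a 2-month and a 4-month interaction coefficient, and the group means are to be plotted, so a reversal would be visible. The information is available; the protocol does not name it as the test.

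Fourth, a reader might infer that the primary error rate is 9.1%. That needs a rule by which either visit counts as success, and the protocol states no such rule. The overall interaction test at a pre-fixed coding holds 5%, and requiring both visits gives about 0.9% when neither has an effect.

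**Conclusion.** The point holds as an error in what the Outcome analysis section states, and it should be fixed. Under either permitted coding, the group x time interaction does not test better MCS at both visits. With categorical time it cannot distinguish sustained, transient and delayed effects of equal size (power 39% to 99% over 0.2 to 0.5 SD, identical across the three). With continuous time it is in effect a test of the 4-month change, with about 5% power for a transient effect.

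The percentages rest on the assumed SD-unit effects, complete data, 140 per arm and ρ = 0.50. The equality across patterns needs only compound symmetry and does not depend on the SD. The 9.1% is conditional: it would apply only if the two visit contrasts were each read at 5% with either one sufficing.

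The documents do not make 2 months the right primary visit. They treat the MCS as the distal outcome, reached through hope, self-efficacy, social support, grief and loneliness, so a later effect is plausible too.

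**What to change.** In the Outcome analysis section:
- Fix time as categorical in advance and drop the plot-based choice. If a linear coding could still be selected, both visit effects would be multiples of one slope and could not be tested separately.
- Replace the sentence on the interaction with two contrasts: the between-arm difference in MCS change from baseline at 2 months (end of access) and at 4 months (two months after access ends).
- Name one as primary in advance. The choice is the sponsor's; end of access is one natural option. Test the other at 5% only if the first is significant.
- Report the overall interaction descriptively, and attach the chosen time point to the MCS in the Outcome measures section.

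The cost is wording, with no added visits or data. Two consequences should be stated openly. An effect at the second-ranked visit alone could not be claimed as confirmatory. The power statement must also be restated, because 89% belongs to a time-averaged difference in proportions and a single-visit contrast has about 74% on the same inputs. The fix does not cause that shortfall: at the equivalent standardized effect, 0.15/√(0.5 × (0.2475 + 0.21)) = 0.314 SD, the 2-df interaction test has about 78%.

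### Covariates enter only after a significant result and only where baseline tests are significant, so chance picks them, no order of precedence is set, and baseline MCS is never used as a covariate

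*Protocol article*

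**What the plan says.** All of this is in the Outcome analysis section of the protocol article.

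- **First model.** "Variables included in the GEE model will be group (intervention, control), time (baseline, 2 months, 4 months), and a group x time interaction term". The interaction is the term "which tests the hypothesis that MT4C-In Care promotes better mental health at 2 months and 4 months". Baseline MCS is therefore one of the three outcome values per participant, not a covariate.
- **Trigger for adjustment.** "If a significant intervention effect is detected in this model, additional covariates (e.g., age, gender) will be added to adjust for statistically significant baseline differences".
- **Choice of covariates.** They are added "to adjust for statistically significant baseline differences observed in demographic characteristics between the intervention and control group". Age and gender are examples only; there is no fixed list. Baseline MCS is not a demographic characteristic, so the rule cannot bring it in.
- **Reach.** Analysis of the five secondary outcomes "will follow the same approach as for the primary outcome", so the rule covers six outcomes.
- **Missing data for the primary outcome.** "We will use multiple imputation to handle missing data and will then analyze each dataset using GEE".

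The section does not say whether the unadjusted or the adjusted result is primary if they disagree. Nor does it tie the triggering effect to one term, although the model contains both a group term and an interaction.

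**The concern.** The article states this rule outright; it is not a detail left to an unseen analysis plan. It has three weaknesses.

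1. **It is one-sided.** Only a positive result is re-examined. If the adjusted model then governs, the rule can withdraw a significant finding but never produce one.
2. **Chance chooses the covariates.** After randomisation, a significant baseline difference is a chance event. It says nothing about whether the variable predicts MCS, which is the reason for adjusting.
3. **There is no precedence.** After a positive first model there may be two estimates and two p-values, and either could be presented as the main result.

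At stake are a primary result that is not fully fixed in advance, across six outcomes, and a covariate rule that leaves out the variable most likely to help: the participant's own baseline score.

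**Working it through.** **Inputs from the documents.** 280 participants, 140 per arm; three measurements; compound symmetry; correlation 0.50; alpha 5%; 30% in group 2; 15% difference; stated power 89% (Power and sample size). Allocation 1:1 (Recruitment and randomization).

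**Assumptions.** The documents give no SD for MCS, so effects are in SD units: 0.25, 0.30 and 0.35, equal at 2 and 4 months. Time is categorical, the link is identity, and outcomes are complete or imputed.

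**1. The plan's own figure.** 89% reproduces as a time-averaged comparison of two proportions, 0.45 against 0.30, two-sided.
- Effective n per arm = 140 / [(1 + 2 × 0.5)/3] = 140 / 0.667 = 210.
- Power = Φ{[0.15 × √210 − 1.96 × √(2 × 0.375 × 0.625)] / √(0.45 × 0.55 + 0.30 × 0.70)} = 89.1%.

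No covariate enters this figure, so it neither supports nor contradicts the adjustment rule.

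**2. Chance flags at baseline.** P(at least one of K independent tests significant at 5%) = 1 − 0.95^K.

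| K | Probability |
|---|---|
| 4 | 19% |
| 6 | 26% |
| 8 | 34% |
| 10 | 40% |

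The Carer demographic form section names eight characteristics as examples: four of the carer (age, gender, language, relationship) and four of the resident (stage, age, gender, time in LTC). K = 8 is therefore a reasonable count, but both the number tested and their independence are assumptions.

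**3. What demographics do to the stated test.** The interaction compares changes from baseline between arms. A characteristic that is constant over time and entered as a main effect shifts all three of a participant's expected values equally, so it drops out of the change. In simulated exchangeable GEE fits (280 participants, three visits, correlation 0.5, effect 0.30 SD, covariates explaining an assumed 20% of variance, complete data, 400 runs):
- interaction estimates with and without covariates agreed to rounding error;
- the SE ratio was 1.000;
- power was 73.5% both ways.

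With 20% dropout and no imputation, power was 69.8% unadjusted and 68.5% adjusted, with an SE ratio of 0.997. There was still no gain.

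**4. What baseline MCS does.** Take outcome variance 1 and ρ = 0.5.

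*Plan (baseline as an outcome).* The two changes from baseline each have variance 2(1 − ρ) = 1.00 and covariance 1 − ρ = 0.50. For equal effects d, the noncentrality of the 2-df test is
(140/2) × d² × 2/(1.00 + 0.50) = 93.3 d².

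*Alternative (baseline as a covariate).* Given baseline, the two follow-up values each have variance 1 − ρ² = 0.75 and covariance ρ − ρ² = 0.25. Noncentrality is
(140/2) × d² × 2/(0.75 + 0.25) = 140 d².

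| Effect (SD) | Noncentrality, plan | Power, plan | Noncentrality, alternative | Power, alternative |
|---|---|---|---|---|
| 0.25 | 5.83 | 57% | 8.75 | 76% |
| 0.30 | 8.40 | 74% | 12.60 | 90% |
| 0.35 | 11.43 | 87% | 17.15 | 97% |

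At a single follow-up the variance factors are 1.00 and 0.75, giving 71% against 83% at 0.30 SD, and 83% against 92% at 0.35 SD.

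**5. Adding baseline MCS without changing the model.** If baseline stays among the outcomes and is also entered as a covariate, it is again constant over a participant's rows and cancels. The interaction estimate and its SE do not change. The gain in step 4 needs baseline moved out of the outcome vector.

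**The case against.** The strongest defence is that the rule does little harm to the test the plan names. The first model and its test term are stated, and the adjusted model follows only a positive result. Read that way, it is a robustness check that can remove a claim but not create one. Because demographic main effects cancel from the interaction, the two models would rarely disagree. Most of this stands, and it rules out three stronger readings.

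- **That the rule wastes power by leaving out demographics.** A reader might infer this from a comparison of a single follow-up outcome. The documents do not support it: step 3 shows no gain for the stated test. Pre-specified covariates would gain power if the effect were read as a difference in post-baseline level (81–82% unadjusted against 85–95% in simulation at 0.30 SD, covariates explaining 10–30% of variance), but the plan names the interaction.
- **That withholding adjustment leaves false negatives from chance imbalance uncorrected.** The group term absorbs a chance difference in level; the test concerns change.
- **That the deciding model is undefined.** This is too broad. What is missing is precedence between two results, and which term counts as the triggering effect.

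The defence has limits. The cancellation is not exact with a non-identity link, with covariate-by-time terms, or with unimputed dropout. The plan leaves the link open, although it plans a reflected transformation for negatively skewed scores so that the identity link can be used. For secondary outcomes the missing-data method is still to be chosen. And a rule that is usually harmless is still a poor way to choose covariates.

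**Conclusion.** The concern holds in a limited form. The adjustment rule is data-driven and one-sided, gives no precedence between adjusted and unadjusted results, and extends to all secondary outcomes. Chance alone would flag at least one of eight independent characteristics 34% of the time. The rule does not by itself reduce the power of the stated interaction test under an identity link with complete or imputed data.

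The avoidable loss of precision comes from keeping baseline MCS as an outcome time point, and the covariate rule never corrects that. Under the plan's own correlation structure the difference is 16 percentage points of power at 0.30 SD (90 − 74), 19 at 0.25 SD and 10 at 0.35 SD. These figures rest on assumed effect sizes, equal effects at both visits, 140 analysed per arm and a correlation of 0.50. The trial is not invalidated, but the change should be made before the data are analysed.

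**What to change.** Delete the conditional sentence and the significance tests of baseline differences. Name one primary model, used whatever its result. Suggested text:

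*The primary analysis is a GEE model for MCS at 2 and 4 months with group, categorical time, group-by-time, baseline MCS as a covariate, and province, carer age and carer gender. Baseline MCS is not an outcome time point in this model. The intervention effect is tested jointly as the group difference at 2 and 4 months (2 df). The model with baseline as an outcome and a group-by-time interaction is reported as a sensitivity analysis. Each secondary outcome is analysed in the same way with its own baseline value.*

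The contrast must be reworded along with the model: once baseline leaves the outcome vector, the interaction alone only compares the effect at 4 months with that at 2 months.

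**Cost.** The model and contrast are rewritten and a few degrees of freedom are used out of 280 participants. No new data are needed: the outcome measures and demographics are already collected at baseline, and recruitment is organised by province.
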